### Primary endpoint

The primary outcome measure is the number of times anxiolytics were used within 28 days.

### Secondary endpoint

Total amount of anxiolytic used (diazepam equivalent)Change in State Trait Anxiety Inventory (STAI) total score from baseline at 28 days.2.1.Change from baseline in state anxiety total score at 28 days.2.2.Change from baseline in trait anxiety total score at 28 days.The STAI is a 40-item self-report scale that assesses the presence and intensity of anxiety symptoms as well as the generalized tendency to be anxious [23]. By asking patients how they feel “right now”, the State Anxiety Scale assessed their present level of anxiety, including their subjective emotions of tension, uneasiness, concern, and activation of their autonomic nervous system. There are 20 elements in total, with values ranging from 0–2. The Trait Anxiety Scale measures characteristics of anxiety propensity that are generally constant, such as overall tranquility, assurance, and security [24]. There were 20 items in total, with values ranging from 0–2. Higher ratings indicate severe anxiety.Change in Self-Rating Depression Scale (SDS) total score from baseline at 28 days.The SDS, which includes 20 items on sadness, crying easily, and sleep disorders, is used to assess patients’ depression and changes in therapeutic processes [25]. The scoring system adopts a 4-level scoring system, among which 10 items are positive scoring and the other 10 items are negative scoring. A score < 53 indicates normal, a score 53–72 indicates depression, and a score > 72 indicates major depression. The severity of the depression increases with score.Change in the General Health Questionnaire 60 (GHQ60) total score from baseline at 28 days.The GHQ60 is a 60-item self-rating scale with a range of 0–60 that assesses physical and mental suffering and the likelihood of developing psychiatric illnesses. A high risk of neurosis is indicated by a score of 17 or above [26].Change in the Pittsburgh Sleep Quality Index (PSQI) total score from baseline at 28 days.A self-rated questionnaire called the PSQI rates a month’s worth of sleep disruption and quality. The seven “component” scores, namely subjective sleep quality, sleep latency, sleep length, habitual sleep efficiency, sleep disturbances, utilization of sleeping drugs, and daytime dysfunction, are derived from the analysis of the 19 individual items. The cumulative score is derived from the summation of the points attributed to each of the seven constituent components. An overall score of 5 or above is indicative of poor sleep quality [27].Number of anxiety attacks.

### Sample size calculation

Among the patients treated by the principal investigators and research assistants at the facilities where this study was conducted, those with anxiety disorders suitable for the study generally used anxiolytic medications 30 times/month. We expected the use of lavender aroma would decrease this frequency to about 10 times/month and assumed that the difference in the mean frequency between the distilled water group and the lavender aroma group would be -10 ± 7.5 times/month. If a two-sample t-test is conducted with a two-sided significance level of 5% and power of 80%, 10 patients per group are required. The total sample size is 30 (15 per group), considering that discontinuation or dropout occurs approximately 30% of the time.

### Randomization

Four weeks after the start date, the patients will be allocated to two groups in a random manner, employing a stratified permuted block approach (stratification factors are the primary illness (GAD or PD)) on REDCap. The results of the assignment will be indicated by a number, and a bottle containing the test solution (lavender aroma essential oil or distilled water) will be provided by the Department of Orthodontics, Kagoshima University Graduate School of Dentistry, where the bottles containing the test solution matching the number will be kept without informing the investigators or patients of the type of test solution.

### Statistical analysis

#### Analysis set

For the next analysis sets, statistical analysis will be done.Full analysis set (FAS)All patients will be regarded as FAS, with the exception of those who received care in flagrant violation of ethical standards, those who were not given the test solution, and those whose data for the key outcome were missing.Safety analysis set (SAS)The SAS will be referred to as the group of patients to whom the test solution was distributed.Per protocol set (PPS)The PPS will be referred to as the group of patients who fall under the FAS but do not match the criteria below.3-1.Patients who fail to satisfy the predetermined inclusion criteria or contravene the established exclusion criteria for this study3-2.Notable departures from the established study procedure3-3.Patients who had not carried a bottle containing the test solution for more than 20 days

#### Summary between treatment groups

For each FAS, patient backgrounds will be tallied by therapy group. For continuous data, summary statistics will be provided, and for categorical data, frequencies and proportions (%) will be shown.

#### Primary endpoint

The primary endpoint analysis will be based on the FAS. A sensitivity analysis will be conducted on the PPS to confirm the robustness of the results. This will be analysed using an analysis of covariance model for the change from the baseline to 28 days in the number of times anxiolytic medication is used, with treatment and the baseline value as covariates.

In case of discontinuation, dropout, the number of times anxiolytics per period will be converted to 28 days for the analysis. Missing values will not be imputed.

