#### Secondary endpoints

Secondary endpoints will be analysed in the same way as that for the primary endpoint.

All statistical analyses will be performed with SAS software (version 9.4; SAS Institute, Cary, NC, USA).

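### Randomisation is stratified by primary illness (GAD or PD) but the ANCOVA leaves it out: if diagnosis predicts the outcome beyond baseline, precision is forgone

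*Protocol article*

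**What the plan says.** In the protocol article, Randomization, patients are allocated four weeks after the start date, "employing a stratified permuted block approach (stratification factors are the primary illness (GAD or PD)) on REDCap". This is the only stratification factor.

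Under Statistical analysis, Primary endpoint, the change in number of anxiolytic uses from baseline to 28 days is analysed by ANCOVA "with treatment and the baseline value as covariates". Diagnosis is not among the terms. Under Secondary endpoints the same model is extended: "Secondary endpoints will be analysed in the same way as that for the primary endpoint". No section puts diagnosis into any model.

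The Sample size calculation assumes a difference between arms that "would be -10 ± 7.5 times/month", and states that a two-sample t-test at a "two-sided significance level of 5"% needs, for "power of 80%, 10 patients per group are required". Allowing for about 30% dropout, the target becomes 15 per group.

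**The concern.** Stratified blocks keep GAD and PD close to balanced between arms, so most of the variation between diagnoses drops out of the true sampling variance of the treatment difference. A model without diagnosis still counts that variation as residual error. If diagnosis matters for the outcome given baseline, the reported standard error is then larger than it should be, confidence intervals are too wide, and the test runs below its nominal 5% level.

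The trial plans 30 patients, perhaps 20 of them evaluable, so precision is scarce. The secondary endpoints inherit the same model. They include the number of anxiety attacks, for which a difference between panic disorder and GAD is plausible.

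**Working it through.** **Inputs from the protocol article.** Difference 10 uses per month, SD 7.5 (reading the ± figure as an SD), two-sided 5%, power 80%, 10 evaluable and 15 enrolled per arm (Sample size calculation); one two-level stratification factor (Randomization); model terms treatment and baseline (Primary endpoint).

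**Assumed, because the documents do not give it.** The residual GAD-PD gap *g* in uses per 28 days, given baseline; the share *p* of GAD patients (0.5 unless stated); normal outcomes; baseline unrelated to diagnosis; blocks of 4, or exact balance within strata.

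**Step 1. The plan's own figure.** The normal approximation gives n = 2(1.96 + 0.84)² × 7.5²/10² ≈ 8.8, so 9 per arm. The exact t-test has 75.7% power at 9 and 80.5% at 10, so 10 per arm is right. Dropout: 10/0.70 = 14.3, rounded up to 15 per arm, 30 in total. The stated sample size reproduces.

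**Step 2. Expected effect on the standard error.** With total SD (given baseline) of 7.5, the ratio of the standard error with the factor to that without it is about √(1 − p(1 − p)g²/7.5²):

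- g = 3: √(1 − 2.25/56.25) = 0.98
- g = 5: √(1 − 6.25/56.25) = 0.94
- g = 7.5: √(1 − 14.06/56.25) = 0.87
- g = 10: √(1 − 25/56.25) = 0.75

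Simulated mean standard errors at 10 per arm agree (without → with): 3.41 → 3.35, 3.42 → 3.22, 3.45 → 2.97 and 3.45 → 2.55. At g = 0 they are 3.40 → 3.42.

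**Step 3. Power and type I error by simulation, 10 per arm.** The plan does not say whether 7.5 includes the spread between diagnoses, so both readings are shown. Entries are without → with the factor.

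| Gap g | Power, total SD 7.5 | Power, within-diagnosis SD 7.5 | Type I error without the factor |
|---|---|---|---|
| 0 | 77.1 → 76.6% | 77.9 → 77.6% | 5.4% |
| 3 | 78.6 → 78.8% | 76.4 → 77.4% | 5.1% |
| 5 | 77.7 → 81.1% | 74.2 → 77.9% | 4.1–4.2% |
| 7.5 | 79.3 → 88.0% | 69.7 → 77.9% | 2.8–3.1% |
| 10 | 81.0 → 95.1% | 62.1 → 77.4% | 1.5–1.8% |

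Runs per setting were 5,000 for total SD 7.5 and 8,000 for within-diagnosis SD 7.5 (6,000 for its gap of 3). Simulation error is about 0.3 to 0.6 points. For gaps of 0 and 3 the type I error is from the total-SD runs only. With the factor in the model, type I error is 4.7% to 5.4% throughout.

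On the second reading the gap is added on top of 7.5, so total SD rises to √(56.25 + g²/4) = 7.9, 8.4 and 9.0 for gaps of 5, 7.5 and 10. Much of the fall to 62% comes from that larger variance.

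**Step 4. Other settings.** At 15 per arm and g = 5, power is 94.3 → 95.7% (total SD 7.5) or 91.0 → 92.6% (within-diagnosis SD 7.5). The gain is 1.4 to 1.6 points, against 3.4 to 3.7 at 10 per arm. At g = 3 the corresponding figures are 92.7 → 93.5% and 93.0 → 93.4%, under one point and close to simulation error. With an 80:20 mix, g = 5, 10 per arm and within-diagnosis SD 7.5, power is 75.4 → 76.3%, a gain of 0.9 points.

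**The case against.** The strongest reply is that nothing in the documents shows diagnosis to be prognostic once baseline use is in the model. The Basis for setting inclusion criteria says only that GAD and PD are the diagnoses met most often in practice. A difference in how often the two groups take as-needed benzodiazepines is largely what the four-week baseline count captures, so the residual gap may be small. Gaps of 5 to 10 uses are 0.67 to 1.33 SDs, and the largest equals the whole assumed treatment effect. Dropouts' counts are also converted to 28 days, so the analysed number may be nearer 15 than 10 per arm, where power is above 88% without the factor even at a gap of 7.5. All of this stands, and it limits the size of the point.

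It does not remove the point. The model terms are stated outright, so this is not a detail left to a statistical analysis plan. The choice does not require knowing the gap: with no gap, adding the factor costs half a point of power or less; with a real gap it recovers something. Baseline use is also a less obvious proxy for diagnosis in some secondary outcomes than in the primary one.

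A reader might infer that the standard errors are certainly too large, that the trial is underpowered, or that its sample size is wrong. The documents support none of these. The first needs a gap they do not report. The second needs a large gap added on top of the planning SD. The third is contradicted by the reproduced calculation. Nor is there any inflation of false positives.

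**Conclusion.** The mismatch between stratified randomisation and an analysis without the stratum is a fact of the text. Its consequence is conditional: if GAD and PD differ in the outcome beyond baseline, the standard error is overstated and the test is conservative. The treatment estimate remains unbiased.

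At 10 per arm and an equal mix, the power forgone is about 0 to 1 point for a residual gap of 0 to 3 uses, about 3 to 4 points for a gap of 5, and about 8 to 15 points for gaps of 7.5 to 10; that last range is an extreme assumption. If 7.5 is the total SD, unadjusted power stays at 77% to 81%, so the planned power is kept and only a possible gain is lost. For the secondary endpoints the direction is the same, but the size was not calculated. This is an efficiency improvement, not a flaw that invalidates the design.

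**What to change.** In Statistical analysis, Primary endpoint, add primary illness (GAD or PD, as recorded for randomisation) as a fixed factor alongside treatment and baseline. State under Secondary endpoints that those models include it too. Make the change before unblinding, so that it cannot look data-driven.

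The cost is one model term and one degree of freedom: at 10 per arm, 0.3 to 0.5 points of power if diagnosis has no residual effect (77.9 → 77.6% and 77.1 → 76.6%), which is within simulation error. The sample size need not change.

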#### Secondary endpoints

Secondary endpoints will be analysed in the same way as that for the primary endpoint.

All statistical analyses will be performed with SAS software (version 9.4; SAS Institute, Cary, NC, USA).

#### Interim analyses

No interim analysis is planned.

### Monitoring

To ensure that this study is being carried out properly, the lead investigator will request that the institution perform monitoring. As a usual practice, the monitoring report will be submitted annually.

### Adverse events

The incidence of adverse events is minimal, and no discernible health or safety concerns have been reported in relation to the participants included in the clinical research. The safety monitoring group will oversee data monitoring. Throughout the course of the 1-week program, any small or significant occurrences related to the intervention or routine care groups will be observed. The chief investigator will review any negative or unexpected consequences.

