## Design

### Study design

This study is a multicenter, double-blind, randomized, and placebo-controlled clinical trial. To compare the effectiveness of treatment with lavender aroma, we will compare two groups of patients: a lavender aroma group and a non-lavender aroma group who were provided with a placebo. Double masking is necessary due to the possibility of changes in medical treatment once the researcher knows the allocation results.

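### The adverse-event paragraph describes a 1-week programme with a routine-care group, but the trial compares lavender with distilled water over an implied 28 days

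*Protocol article*

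**What the plan says.** The protocol article gives one rule for observing adverse events, in the Adverse events section: "Throughout the course of the 1-week program, any small or significant occurrences related to the intervention or routine care groups will be observed". The same section opens with "The incidence of adverse events is minimal, and no discernible health or safety concerns have been reported", assigns data oversight to a safety monitoring group, and has the chief investigator review untoward findings.

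The rest of the article describes a different structure:

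- **Arms.** Study design names "a lavender aroma group and a non-lavender aroma group who were provided with a placebo". Interventions and Randomization confirm that the comparator is distilled water, supplied in numbered bottles under masking.
- **Period.** The endpoint definition reads: "The primary outcome measure is the number of times anxiolytics were used within 28 days". The score changes under Secondary endpoint are also taken at 28 days. The primary analysis uses the "change from the baseline to 28 days in the number of times anxiolytic medication is used", and for patients who stop early "the number of times anxiolytics per period will be converted to 28 days for the analysis".
- **Per-protocol rule.** Analysis set removes "Patients who had not carried a bottle containing the test solution for more than 20 days".
- **Safety as an aim.** The end of the Background and the start of the Discussion both give safety as an aim beside efficacy. Analysis set defines a safety set of everyone who was given the test solution.

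**The concern.** The safety paragraph conflicts with the rest of the protocol on two points: how long patients are observed, and which groups are observed. Both determine what a safety comparison can support.

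A site that followed the paragraph as written would have no instruction to record adverse events after the first week. The paragraph also does not name the distilled-water group, the only group against which the lavender arm's events can be compared. The safety analysis set would then include every patient given a bottle, with events recorded for only part of the time those patients had it. A statement that sniffing lavender was well tolerated would rest on an observation rule that does not match the trial.

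**Working it through.** **The plan's own computed figure.** The only calculated number in the article is the sample size, and this point does not depend on it. It reproduces. For a difference of 10, an SD of 7.5, two-sided 5% and 80% power, the two-sample t-test needs 9.89, so 10 per group (power 0.805 at 10). Allowing for 30% dropout, 10 / (1 − 0.30) = 14.3, so 15 per group and 30 in total.

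**Step 1: the arms.** Adverse events refers to occurrences "related to the intervention or routine care groups will be observed". Study design, Interventions and Randomization describe only lavender and distilled water. Routine care appears nowhere else as a group, so the two descriptions cannot both be right.

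**Step 2: the period.** No sentence says that treatment lasts 28 days, and the schedule figure is not shown in the text reviewed. The length is therefore inferred from three places:

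- the primary and secondary endpoints are taken within or at 28 days;
- the primary analysis runs to 28 days and scales shorter records up to 28;
- the per-protocol rule counts carrying days against a threshold of 20, which cannot be applied to a 7-day programme (20 / 7 = 2.9 weeks).

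All three are incompatible with one week. The first two point to 28 days, and nothing supports another length.

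**Step 3: the size of the mismatch.** Let W be the stated window and T the test-solution period, both in calendar days. The share outside the window is (T − W) / T.

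| Period T | Window W | Days outside | Share outside |
|---|---|---|---|
| 28 (implied by endpoints and analysis) | 7 | 21 | 21/28 = 75% |
| 20 (carrying threshold, as a lower figure) | 7 | 13 | 13/20 = 65% |
| 28, with a window matched to it | 28 | 0 | 0% |

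The 75% is for a patient who completes 28 days; a patient who withdraws earlier has a smaller share outside.

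**Step 4: is there another window?** The safety set in Analysis set is defined by who received the test solution and carries no observation period. Monitoring deals with annual reports. No other section states when adverse events are observed.

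**The case against.** The strongest reply is that the sentence is stray wording and not an operative 7-day rule. It promises observation throughout the programme, so if the programme length were corrected, observation would cover the whole period. This is plausible, and it limits what the 75% can mean. It does not remove the need for correction, because the article gives no other window and the group names are wrong as well.

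Several stronger readings are tempting but not supported:

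- *About 75% of adverse events would be missed.* This needs both a literal reading and a constant event rate, which no section supports. Drops are used when the patient is anxious, so calendar days are not a measure of exposure either.
- *Only events judged causally related are captured.* The sentence ties occurrences to groups of patients and covers both small and significant ones. It is not clearly a causality filter.
- *The result is announced in advance.* The study dates run from September 2018 to March 2024, so the statement that incidence is minimal could be a status report from a trial under way, or background. It is ambiguous, not demonstrably a pre-stated result.
- *Delayed reactions to the oil, or events following changes in benzodiazepine use, would be lost.* Nothing in the article describes either as expected.
- *The patient diary already captures adverse events.* It is described only as recording benzodiazepine and aroma use.

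It is also fair to note that the section provides for a safety monitoring group and chief-investigator review, and that no safety variable is listed among the primary or secondary endpoints.

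**Conclusion.** The contradiction stands on both counts: one week against an implied 28 days, and routine care against distilled water. Taken literally, the stated window covers 7 of 28 calendar days, leaves 21 (75%) outside, and does not name the placebo arm. That figure rests on three assumptions: the sentence is applied as written, the test-solution period is 28 days, and the patient completes it.

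This is a conflict within the article, not detail left to a fuller protocol or analysis plan. It concerns the only stated rule for observing adverse events in a trial that aims to assess safety. The consequence is confined to what the safety analysis set can support; sample size, power and the primary analysis do not change. Whether collection in practice stops at one week cannot be determined from the document.

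**What to change.** Reconcile the Adverse events section with Study design, Interventions, Primary endpoint and Analysis set:

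1. Replace the 1-week programme with the actual test-solution period, so that adverse events are observed from distribution of the bottle to the end of the 28-day period or withdrawal.
2. Replace the routine-care wording with the two arms of the trial, lavender and distilled water.
3. State that adverse events will be compared by arm in the safety analysis set.
4. Say whether the sentence on minimal incidence is background or a status report from the ongoing trial, so that it is not read as a result.

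The cost is small: one paragraph, and making adverse-event capture explicit at the 28-day assessment that already provides the secondary scores. If patients have already been followed, the report should state the window and groups actually used.

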## Discussion

The objective of this study is to examine the effectiveness and safety of olfactory exposure to essential oil fragrance among individuals diagnosed with anxiety disorders, with the aim of establishing a dependable and secure alternative and adjunctive therapeutic approach for anxiety management in this population. Lavender was taken as a starting point for exploring the use of essential oil fragrances as potential anxiolytic treatments, because a systematic review of aromatherapy on anxiety clearly indicates that it is the major fragrance [28]. Considering this objective, the placebo should meet the following criteria: 1) Be indiscernible from its appearance, i.e., a colorless clear liquid; 2) Having no fragrances. Therefore, our placebo of distilled water is justified. In fact, a systematic review of lavender as a potential anxiolytic supports that using distilled water as a placebo is appropriate [29].

However, there are some limitations to be considered. First, it should be noted that secondary endpoints of STAI, SDS, GHQ60, and PSQI are subjective. Therefore, patients’ objective psychological states or sleep qualities, such as functional magnetic resonance imaging, heart rate variability, or polysomnography might strengthen our findings. Because these were not the primary endpoint, we do not perform further objective assessment. Second, the primary endpoint of the number of times anxiolytics used is not completely objective. Although the possibility may not be high, we should be cautious about the accuracy of patients’ reporting of their anxiolytics use.

Last but not least, limitations of statistical analyses should be seriously discussed. The difference of primary endpoint in the mean frequency of benzodiazepine use between the distilled water group and the lavender aroma group of -10 ± 7.5 times/month was derived from a simple assumption. Therefore, we cannot deny the possibility of manipulating the sample size. Nonetheless, this assumption was based on our clinical experience of patients with mood disorders by the intervention of complementary medicine, such as mindfulness. Another statistical limitation lies in imputation. If missing values tend to appear in one common characteristic of patients, using imputation to handle such patients could reveal significant insights. However, because the sample size was calculated considering dropout rate of 30%, and such analysis can be performed separately, we decided to perform no imputation.

Considering aforementioned limitations, if the use of benzodiazepines could be reduced by sniffing inexpensive and safe essential oils, including lavender, this would contribute not only to the risks associated with benzodiazepine drug use, but also to the health care economy. In addition, since sniffing aromas is simpler than taking medications with drinking water, the use adherence is likely to be higher and it could be added as a standard treatment.

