**Methods:**

This study is a multicenter, double-masked, randomized, placebo-controlled clinical trial. The study will recruit patients aged 20–59 years old with generalized anxiety disorder and panic disorder among anxiety disorders. The bottle containing the test solution (lavender aroma essential oil or distilled water) will be given to the patients. Patients will carry the bottles with them in their daily life and use the drops on tissue paper when anxious. The primary endpoint is the number of times anxiolytics used in 28 days.

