The aforementioned research may suggest the possibility of aromatherapy as a treatment for anxiety disorders. However, these do not include studies of inhaling or sniffing essential oil. While inhaling essential oils changes moods in healthy volunteers [19], a study on women undergoing abortions indicates that aromatherapy cannot be substituted for anxiolytics [20]. Therefore, anxiolytic effects of inhaling essential oils still need to be elucidated. Additionally, it should be noted that inhaling and sniffing may exhibit different effects because inhaling essential oil means the oil is gas while sniffing means the oil can be in various forms, such as liquid or solid.

In summary, to the best of our knowledge, the possibility of chronic exposure to sniffed essential oil as an aromatherapy for treating anxiety disorders has never been evaluated. Therefore, the effect of sniffing fragrance in aromatherapy should be elucidated first before delving into which essential oils show an anxiolytic effect.

In this study, starting with lavender as our initial focus, we will investigate the efficacy and safety of sniffing lavender aroma in patients with anxiety disorders, aiming to develop a reliable and safe alternative and complementary treatment.

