#### Exclusion criteria

Patients who fell into the following criteria below are excluded from the study.Patients who are diagnosed with significant physical and mental health issues by the physician in charge.Patients who are pregnant, possibly pregnant, within 28 days postpartum, or are breastfeeding.Patients who are diagnosed with any olfactory dysfunction or chronic nasal obstruction.Patients with dilated thoughts of death.Patients using anxiolytics other than benzodiazepines as an abortive medication for anxiety attacks.Any patients deemed ineligible by the principal investigator or sub-investigator for this study were excluded.

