**Fig. 1 Fig1:**
[figure not shown]
Flowchart of the study schedule. GAD = generalized anxiety disorder; PD = panic disorder; STAI = State Trait Anxiety Inventory; SDS = Self-Rating Depression Scale; GHQ60 = General Health Questionnaire 60; PSQI = Pittsburgh Sleep Quality Index

Lavender aroma (*L. angustifolia* ssp. Angustifolia (Pranarom International, Ghislenghien, Belgium) or distilled water is used as the test solution, which is stored in a 10 ml glass bottle with a drop stopper (Pranarom International). The bottle containing the test solution (lavender aroma essential oil or distilled water) will be given to the patient without informing them of the type of test solution. Patients will be asked to carry the bottles with them daily at all times and use the drops on the tissue paper when anxious. The patients will be instructed to maintain a diary in which they will record details on their benzodiazepine medication and aroma usage (Supplementary Fig. 1).

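### The trial is labelled double-masked, but patients sniff either lavender oil or odourless water, so they cannot be assumed masked after first use of the bottle

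*Protocol article*

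**What the plan says.** The Methods part of the Abstract describes a "multicenter, double-masked, randomized, placebo-controlled clinical trial", and Study design uses the term double-blind. The reason given there concerns the researcher: "Double masking is necessary due to the possibility of changes in medical treatment once the researcher knows the allocation results".

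The aim stated in Background is this: "we will investigate the efficacy and safety of sniffing lavender aroma in patients with anxiety disorders". Under Interventions, patients carry a 10 ml bottle of lavender oil or distilled water and are told to "use the drops on the tissue paper when anxious". On concealment from the patient, the same section says: "The bottle containing the test solution (lavender aroma essential oil or distilled water) will be given to the patient without informing them of the type". Randomization adds that bottles are numbered, are kept and supplied by a separate department, and that neither investigators nor patients are told the contents.

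The Exclusion criteria remove "Patients who are diagnosed with any olfactory dysfunction or chronic nasal obstruction". The Inclusion criteria require that patients have never used aroma products. The Discussion states the two placebo requirements, "Be indiscernible from its appearance, i.e., a colorless clear liquid; 2) Having no fragrances", and concludes from them, with support from a cited systematic review, that distilled water is justified.

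The primary endpoint is the count of anxiolytic uses in 28 days. Under Interventions, benzodiazepine use is recorded in a diary that the patient keeps. The Discussion lists four limitations: subjective secondary questionnaires, accuracy of patients' reports of anxiolytic use, the basis of the sample-size assumption, and the absence of imputation. Loss of masking is not among them.

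**The concern.** A placebo masks the patient when she cannot tell it from the active product in use. Here the liquids match to the eye but differ in smell, which is what the patient is asked to perceive. The exclusion for smell disorders selects patients who can perceive it.

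The outcome is exposed to this. The primary endpoint depends on the patient's decision to take a benzodiazepine and on her own record of it, and both can respond to what she believes about her bottle. STAI, SDS, GHQ60 and PSQI are self-rated as well. Expectation of benefit with a scented bottle, or disappointment with an unscented one, would move these outcomes in the direction that favours lavender. A significant difference could then not be reported as a patient-masked, placebo-controlled effect of lavender.

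**Working it through.** **Step 1. What each safeguard protects.**

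- REDCap allocation, numbered bottles and a separate department (Randomization) keep the next assignment unknown and the label uninformative. This is allocation concealment, and it is unaffected.
- Not telling patients or investigators the contents (Interventions, Randomization) withholds information, but it does not remove the odour.
- Matched appearance (Discussion) masks by sight only.
- The second placebo requirement, no fragrance, guarantees a difference in smell between the arms.
- No history of aroma use (Inclusion criteria) may stop a patient naming lavender. It does not stop her noticing a scent or its absence.

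Nothing described in the article masks the patient once a drop is on the tissue.

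**Step 2. The plan's own figure.** Inputs from Sample size calculation: difference 10, SD 7.5, two-sided 5%, power 80%.

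- Standardised difference: d = 10 / 7.5 = 1.333.
- Two-sample t-test with n per arm: df = 2n − 2, noncentrality = d × √(n/2).
- At n = 10: noncentrality = 1.333 × √5 = 2.98, power 80.5%. At n = 9, power is 75.7%. So 10 per arm is reproduced.
- Dropout: 10 / (1 − 0.30) = 14.3, rounded up to 15 per arm, 30 in total. Reproduced.

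**Step 3. Scale of an expectancy shift (assumption).** The documents give no figure for expectancy. Let lavender have no true effect, and let knowing scent from no scent shift the difference in counts by b uses per 28 days. With the same test and SD, d = b / 7.5, and the chance of p < 0.05 is the two-sided rejection probability of the noncentral t.

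- b = 3: d = 0.40. Noncentrality is 0.40 × √5 = 0.89 at n = 10 and 0.40 × √7.5 = 1.10 at n = 15.
- b = 5: d = 0.667. Noncentrality is 0.667 × √5 = 1.49 at n = 10 and 0.667 × √7.5 = 1.83 at n = 15.

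| Assumed shift b | Share of planned difference of 10 | p < 0.05 at 10 per arm | p < 0.05 at 15 per arm |
|---|---|---|---|
| 0 | 0% | 5% | 5% |
| 1 | 10% | 5.9% | 6.4% |
| 2 | 20% | 8.7% | 10.9% |
| 3 | 30% | 13.5% | 18.5% |
| 4 | 40% | 20.4% | 29.2% |
| 5 | 50% | 29.2% | 42.2% |
| 7.5 | 75% | 56.2% | 75.3% |

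Both columns are needed. The plan expects about 10 evaluable patients per arm after dropout, but the primary analysis converts counts from patients who stop early to 28 days, so the number analysed may lie between 10 and 15. The planned analysis is an ANCOVA on change with baseline as covariate, not this t-test. If baseline adjustment brings the residual SD below 7.5, the same shift gives higher rates than those shown.

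**The case against.** The odourless comparator is deliberate. Background says the effect of sniffing a fragrance should be settled before asking which oil works, and the Discussion derives an unscented placebo from that aim. This stands as a reason for the comparator, and the cited review may support water as a control. Neither makes a scented and an unscented liquid alike to someone sniffing them, so neither supports the masking label.

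That every patient certainly knows her arm is an inference. The article reports no test of masking, and the consent text is not available here. A patient given water notices no scent, but whether she reads that as being in the control group depends on what she was told. This stands: the claim should be that patients very probably can tell, not that close to all of them guess correctly.

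A reader might also infer that the protocol contradicts its own reason for masking. The documents do not support that. Study design speaks of the researcher's knowledge, and Randomization partly protects it. Physician masking is at risk only if patients disclose what they smell or the scent is noticed.

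Finally, the Discussion already calls the primary endpoint not fully objective. It does so for accuracy of reporting only. Differential reporting or behaviour because the arm is perceptible is a separate problem and is not stated.

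**Conclusion.** The point holds for patients. The article claims masking that the described intervention very probably does not provide after first use, and it omits this from a limitations section that discusses both the placebo and the self-reported endpoint. Allocation concealment is sound, and physician masking may hold.

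The consequence is for interpretation: the trial can compare lavender scent with no scent, expectancy included, but cannot separate the two. The size is unknown. If expectancy alone moved the count by 3 to 5 uses per 28 days (30% to 50% of the planned difference), the false-positive rate would be about 13.5% to 29.2% at 10 per arm and 18.5% to 42.2% at 15 per arm. Those figures rest on an assumed shift, the plan's SD of 7.5 and an unadjusted t-test. The conclusion about masking does not depend on them.

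A reader might go further and call the comparator wrong. The documents do not support that, because an odourless control fits the authors' stated question.

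**What to change.** 1. Replace the double-masked and double-blind label. State that patients cannot be assumed masked after first use and that investigators are not told the allocation. Claim masking of the statistician or data handlers only if it is true, since the article does not say so.
2. Add loss of patient masking to the Discussion as a main limitation.
3. Restrict the conclusion to the effect of a lavender scent versus no scent, including expectancy.
4. For patients still to be treated, record expectation of benefit before allocation. At day 28, ask patient and physician to guess the allocation. Report both by arm.
5. For the same patients, ask that the bottle not be opened and the scent not be mentioned at study visits, leaving the instruction on use when anxious unchanged.

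Items 1 to 3 are wording only and can be made at any stage. Items 4 and 5 cost a few questionnaire items and one instruction. Because the stated study dates run from September 2018 to March 2024, they cannot be applied to patients already treated. No change of comparator is needed. The price is a less favourable design label.
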